### Oversight and Review of Adverse Events

Every two months, the entire investigative team from Columbia University and Kazakhstan will review all adverse event data to date to determine if systematic trends exist among adverse event data to warrant changes to study protocols and procedures. Any proposed changes will be reviewed with staff at the study site, and, if needed, an external consultant (e.g., other senior investigators conducting federally-funded research on drug abuse). Approval for changes in study protocol or materials will then be obtained from the IRBs at Columbia University and from the Kazakhstan School of Public Health in Kazakhstan. After approval, the NIDA Project Scientist will be notified, and changes will also be reported in the annual progress report submitted to NIDA. The investigative team from GHRCCA at Columbia University will also conduct systematic analyses of adverse event data (e.g., associations

among frequency, type, severity of adverse events; participant characteristics; and operational aspects of research such as time-point) to inform future studies as well as recognize that such activities represent a potentially under-researched area of inquiry and scientific endeavor unto itself.

## **9. TRAINING AND QUALIFICATIONS OF STAFF**

All research and TP staff involved will have completed the Columbia University Office of Projects and Grants' Human Subjects training course that will be translated into Russian, which has received approval from DHHS Office of Human Research Protections to supersede the NIH training course on Protection of Human Research Subjects. The Columbia University training also includes compliance with the Health Insurance Portability and Accountability Act of 1996 (HIPAA). As part of GHRCCA's standard operating protocols, all GHRCCA field, quality assurance, and management staff must complete an intensive, day-long, structured training program on detecting, addressing, and reporting adverse events before they are allowed to participate in any research.

Training which will be conducted by Drs. [name], [name], [name] and [name] will focus on: (1) ethical issues in research, confidentiality and learning about potential adverse events that may be experienced; (2) establishing and maintaining rapport with participants; (3) obtaining informed consent from participants; (4) addressing participants' concerns with confidentiality and handling sensitive situations; (5) obtaining accurate tracking information; (6) managing distress and conducting crisis and enhanced referrals; and (7) detecting, handling, and reporting adverse events.

The training will also cover how to handle challenging situations, including how to respond to distressed participants and participants who are experiencing life threatening situations. Also, each research study at GHRCCA conducts an annual 3-hour meeting, first reviewing human subjects protection principles and study-specific procedures, followed by discussion of adverse events for the study over the past year, and role-play exercises which provide a "booster" to enable staff to handle future adverse events knowledgeably, appropriately, and expeditiously.

### Qualifications and Training for Research Assistants

RAs will have a bachelor's degree and/or significant experience in conducting health and/or drug abuse research. RAs will have the capacity to conduct assessments and interview participants about sensitive topics (e.g., sexual behavior, IPV). Interviewers will receive about 40 hours of training, observation, and role-play before administering the ACASI, biological specimen collection, and pre-test counseling procedures.

Interviewer training will include (1) ethical issues in research; (2) establishing and maintaining rapport with participants and different strategies of recruitment; (3) obtaining informed consent; (4) handling sensitive situations; (5) administering screening interview and determining eligibility; (6) administering ACASI and assisting participants; (7) obtaining accurate tracking information and retention strategies; and (9) managing distress and conducting crisis and enhanced referrals. The Project Director will meet weekly with RAs to reinforce adherence to study protocols and to develop consistent procedures for handling unanticipated scenarios/situations.

### Qualifications, Training and Supervision of the Nurses in the TPs

For this study, nurses will be responsible for conducting rapid testing in TPs for HIV. The Project Director will participate in biweekly conference calls with Drs. [name], [name], [name] and [name] to monitor adherence to biological testing and treatment protocols.

### Timeline of Trainings for BRIDGE Staff

We will provide a 7-day training for TP outreach workers, case managers, and nursing staff who will implement and oversee integrated BRIDGE components in each city one month prior to BRIDGE rollout. New staff will be invited to attend subsequent trainings in each city. Nurses from the Trust Point will provide weekly supervision to TP staff on SNS and ARTAS activities. The local supervisor will provide bi-weekly supervision to TP nurses and conduct the community of practice monthly meetings. We developed structured manuals and implementation protocols for all BRIDGE activities. The Study Project Director with input from [name] will be available to

provide technical assistance to supervising nurses. Data on number and type of technical assistance contacts will be collected for Aim 4.

## 10. BENEFITS, SUSTAINABILITY AND DISSEMINATION

### 10.1. BENEFITS

The main benefits to PWID of participating in BRIDGE intervention activities are having access to HIV testing and care and obtaining services, treatment, and care. The main benefits to trust point nurses, social workers and outreach workers are gaining new counselling and communication skills through the BRIDGE intervention training.

Impact of Collaborative Quality Improvement Across Components: Following implementation science best practices, we will provide continuous feedback on process measure performance to service providers in AIDS centers and TPs, rather than restrict availability of these data until the study's conclusion. We will also train case managers and AIDS center nurses on how to use these results in quality improvement across the HIV treatment continuum. We will bring a new way of delivering HIV prevention to TPs via integrating HIV care into their programs and will train the staff to use this approach in delivering the intervention.

### 10.3. DISSEMINATION OF FINDINGS

With completion of the BRIDGE stepped wedge trial, we will assess outcomes and contextual factors critical to successful implementation in a range of settings in Kazakhstan. To disseminate study findings we expect to write manuscripts on (1) Outcomes of study for Aims 1 and 2, (2) Description of BRIDGE and intervention (3) Implementation Facilitators and Barriers using mixed methods data from Aim 3; (4) Cost-Effectiveness of BRIDGE; and (5) Multi-level factors influencing sustainability of BRIDGE. If study results suggest BRIDGE effectiveness, this model of service integration can be used to advance HIV service delivery for PWID in Central Asia, Eastern Europe and Asia with injection-driven HIV epidemics. We will hold a scientific meeting with key stakeholders in each city to present the study findings and develop a strategic plan to scale up BRIDGE. Study findings will be disseminated through local, national, and international meetings, conferences and publications in English, Russian, and Kazakh. We will capitalize on socio-technological trends that can increase the reach and impact of study findings, such as open access publication, webinars, files and videos, social media, and metadata (e.g., search engine optimization).

## **Appendix A: AppSheet Protocol**

This protocol describes all procedures and systems used in the AppSheet component of data collection for program-level outcomes for the BRIDGE study. For complete study procedures, please see the Stand-Alone Protocol.

### **PURPOSE OF APPSHEET DATA COLLECTION**

The purpose of AppSheet data collection is to collect **de-identified** aggregate-level data on services received by PWID at BRIDGE trust points and city AIDS Centers in each of our four study sites.

The data provided in this tracking system will be used to test the hypotheses of Study Aims 1 and 2. Study Aim 1 seeks to evaluate the effectiveness of implementing BRIDGE's enhanced service integration approach in Trust Points (TPs) on linking HIV-positive People who Inject Drugs (PWID) to HIV care. Study Aim 2 seeks to evaluate the effectiveness of BRIDGE's enhanced service integration approach on increasing HIV testing in TPs and increasing retention in HIV Care Clinics. This tracking system allows us to monitor "linkage" to care and repeated testing visits among PWID by tracking what services PWID receive.

## **OVERVIEW OF ASSESSMENTS**

AppSheet Data Collection consists of four surveys: one pre-implementation and one post-implementation survey that will be completed by trust point nurses and one pre-implementation and one post-implementation survey for AIDS Center nurses. Trust point nurses will receive compensation from BRIDGE study for collecting these data. They will receive training and supervision on use on all AppSheet Data Collection procedures by BRIDGE research staff. Prior to using AppSheet Data Collection survey, all TP nurses will complete Human Subjects Training course and submit their certification.

### Pre-Implementation Survey

Prior to the start of the intervention in each city, the nurse will administer a pre-implementation survey on an electronic tablet to every client who comes to the trust point or AIDS Center. The Pre-Implementation survey will contain questions regarding which services were administered to the client. No personally identifiable information will be collected. Responses will be linked to a unique 6-digit study ID number for each client, which will consist of a code that signifies the trust point where it is created, and a random number. This ID will not be linked to the participant's name or any other PII or PHI information). The Pre-Implementation Survey will take approximately 5 minutes to complete.

### Post-Implementation Survey

Following the start of the intervention in each city, the nurse will administer a post-implementation survey on an electronic tablet to every client who comes to the trust point or AIDS Center. The Post-Implementation survey will contain questions regarding which services were administered to the client, including, in the Trust Point Nurse surveys, the BRIDGE intervention components of SNS recruitment (whether the client was referred as part of the peer recruitment strategy) and ARTAS (whether the client completed an ARTAS session during that visit). No personally identifiable information will be collected. Responses will be linked to a unique study ID number for each client. The Post-Implementation Survey will take approximately 5 minutes to complete.

Study sites will switch from the pre-implementation to the post-implementation survey once BRIDGE is rolled out in their city. Due to the stepped-wedge design of BRIDGE, each study site will make this switch at a different time. A graphic is provided below, where month 13 (the start of data collection) is November 2016.

[figure not shown]

### CLIENT CONSENT

Before enrolling a client into the AppSheet system, the trust point nurse must conduct informed consent with the trust point clients. As trust point services are provided anonymously, we have requested a waiver of documentation of consent.

Participants will undergo a formal informed consent process, where they will be informed that by giving consent, they are releasing their information or data about services they receive at trust points and AIDS centers as part of the research study. The informed consent form details the data that will be collected [information about the services provided to them each time they come to the trust point or AIDS Center, such as the number of syringes given, tests received (including HIV rapid tests, STI tests, viral load, and CD4 count), participation in current and/or future programming (including rapid HIV testing and the ARTAS case management sessions in the BRIDGE intervention), and the other health care facilities they were referred to, such as polyclinics, NGOs, or TB centers.],

and that all data will be de-identified prior to collection. Participants will be introduced to the AppSheet system, and all data collection procedures involving this system will be described to them in detail. The consent form will also detail all potential risks and benefits to the participant in agreeing to release their data to the BRIDGE study, and all measures to protect their confidentiality will be explained in detail.

The nurse will only proceed to enroll the client into the AppSheet system if the client provides verbal consent.

## **CLIENT ENROLLMENT**

BRIDGE trust points are asked to enroll as many PWID clients as possible in the AppSheet system over the course of the study. “Enrollment” means that the process is explained to PWID clients, they agree to take part (as data is de-identified and void of PII or PHI identifiers, we are requesting a waiver of consent for enrolling AppSheet participants in this portion of the study (as discussed in the main protocol), and they receive an ID card with a unique ID in the form of a barcode (detailed below). In discussing the system with their clients, trust point nurses should raise the following points:

- This system is an innovative and simple way of tracking trust point clients that is being implemented at this trust point
- The system is created and monitored by a research study which is interested in how often trust point clients receive services and which services they receive
- Clients will be assigned a random ID number. The nurse is the only person who can connect this number to their UIC code (the code by which clients are registered at the trust point - see below)
- Clients should hold on to their ID card and present it every time they come to the trust point to receive needles/syringes or testing, or every time they go to the AIDS Center for any reason
- If they lose their ID card, the nurse can replace it; they will need to come back to the trust point and provide their UIC number again.

## **ID NUMBERS**

ID numbers are assigned by the nurses at BRIDGE trust points. Starting in November 2016, trust point nurses in BRIDGE trust points will begin to assign unique 6-digit ID codes to their regular PWID clients. The 6-digit code will consist of the following components:

Digits 1-3: code of the trust point where the ID is being assigned

Digits 4-6: random digits (we suggest 001, 002, 003, etc.)

The nurse will be responsible for keeping a list of all ID codes assigned. Trust point services in Kazakhstan are anonymous, and in regular operations, nurses track clients using a standardized “unique identification code” or UIC. The nurses at BRIDGE trust points must keep a master list of BRIDGE study codes and UICs. If a client should lose their ID card (described below), the nurse can check this record and provide him with a new one based on his/her UIC.

This ID number will be converted into a scan-able bar code format and printed on a small laminated ID card that can be attached to the client’s keychain.

This bar code can be scanned by a tablet or smartphone within an AppSheet survey, saving time and reducing the change of error. The keychain format is intended to prevent loss of the ID card.

## **DATA COLLECTION USING APPSHEET**

Nurses at the trust points and AIDS Centers will collect pre- and post-implementation assessments from study participants using a secure, encrypted, password-protected tablet. No personally identifiable information or

personal health information will be collected. To minimize data entry errors and missing data, the data collection program installed on the tablet (AppSheet) will be programmed with automatic skip patterns, requirements that each item be answered or refused, and acceptance of only values within the appropriate range of responses for that item. To ensure that the correct assessment and procedures are completed at each study visit, the data collection program installed on the tablet will be programmed to include only the study assessments and procedures relevant to that visit. All data collected on the tablet will be time- and date-stamped, and uploaded to the study server.

## **DATA SAFETY AND SECURITY**

A number of steps are taken to ensure anonymity and confidentiality of the data collected through the AppSheet System.

As trust points already provide services anonymously, through a UIC that has no relationship to any PII indicators, the assignment of an extra ID for identification within the AppSheet system represents a second layer of protection. Only the trust point nurse will have access to the list that links the AppSheet ID to their trust point UIC, and it will be stored in paper format in a locked cabinet in the trust point.

The ID cards that clients of BRIDGE TPs will be given will contain no identification information, and no indication of the participant's participation in the BRIDGE project. Should the QR code on the card be read by an outside source, the 6-digit ID would be meaningless.

All data from the data collection program installed on the tablet (AppSheet) will be collected electronically on password protected and encrypted tablets. Data and subsets of data can be limited by user, and only authorized study staff will have access to the data. Data on the tablets will be electronically transmitted through an encrypted protocol to a secure, remote server run by AppSheet. This data contains no PHI or PII only information about services received by assigned AppSheet ID number. Only authorized users will be able to log into the AppSheet server to view and download data for analysis. The server will maintain an audit trail of all log-ins, edits, and log-outs. The data will be automatically deleted from the tablet once the upload is complete and the server will send an automatic email to the US study coordinator indicating that new data have been uploaded. Access to the data collected on the tablets and stored on the AppSheet server will be limited to only those study personnel with data access rights. The US study coordinator will monitor the study server weekly to ensure that the data collected and uploaded to the server are complete and to monitor for suspicious data activity.

## **Appendix B: AIDS Center Semi-annual report protocol**

This protocol describes the procedures for preparation of the AIDS Center Semi-Annual Report.

### **PURPOSE OF REPORT**

The purpose of this report is to collect de-identified epidemiological and laboratory data on all HIV-positive people who inject drugs (PWID) served by an AIDS center in each of our four study sites.

The data provided in this report will be used to test the research question related to Study Aim 2, which seeks to evaluate the effectiveness of BRIDGE's enhanced service integration approach on increasing retention in HIV Care Clinic, initiating ART, and increasing adherence to HIV treatment regimens and virologic suppression. By comparing epidemiological and laboratory data between BRIDGE trust points and non-BRIDGE trust points, we will be able to evaluate the effects of implementing the BRIDGE intervention in a trust point.

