### 2.4. STUDY ANALYSES

#### *Data analyses by study aim*

To test Aim 1 hypotheses, we will compare data on service linkage outcomes during post-intervention to service linkage outcomes during pre-intervention. Data for Aim 1 will be obtained from the AppSheet tracking system and process measures on ARTAS sessions.

For Aim 2, we will compare data on HIV testing in TPs, retention in HIV care, ART initiation, ART adherence, and viral suppression during post-intervention to these same data during pre-intervention. Data for Aim 2 will be obtained from the AppSheet tracking system and the AIDS Center Semi-Annual Report.

| Table 1: Measurement of Study's Outcome Variables           |                                                                                    |                                            |                                                 |
|-------------------------------------------------------------|------------------------------------------------------------------------------------|--------------------------------------------|-------------------------------------------------|
| Variable                                                    | Instrument/Measure                                                                 | Time point(s) a                 | Source                                          |
| Program Data                                         |                                                                                    |                                            |                                                 |
| PRIMARY OUTCOME: HIV-positive TP clients accessing HIV care | # and % of HIV-positive clients who visit HIV clinic $\geq 1$ time in past 90 days | Ongoing (checked quarterly)                | AppSheet tracking system                        |
| HIV-positive TP clients retained in HIV care                | # and % of HIV-positive clients who visit HIV clinic $\geq 3$ time in past 90 days | Ongoing (checked quarterly), semi-annually | AC semi-annual report, AppSheet tracking system |
| HIV testing at TP                                           | # and % of TP clients who have received an HIV test at TP                          | Ongoing (checked quarterly)                | AppSheet tracking system                        |

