Analysis of Program data: Formal hypothesis testing based on program data will test for differences in outcome measures obtained during the pre-intervention period (i.e., time points before BRIDGE is implemented in a city) versus periods when BRIDGE is implemented. We will employ permutation tests (a.k.a. “randomization tests”) for significance testing because of concerns that the distribution of measures may not be approximated well by a small sample size (i.e.,  $N=24$  TPs). In experimentally controlled trials with small sample sizes, permutation tests have been shown to be superior to parametric tests. As a heuristic and non-parametric approach, permutation testing more accurately estimates the nominal type I error rate for cluster randomized clinical trials with small sample sizes and with measures that may not be normally distributed compared to candidate parametric procedures. Strong hypothesis testing in this manner involves permuting the BRIDGE implementation status of each time point; since the time period “assignment” (pre-implementation vs. BRIDGE) is allocated based on city, permutations will account for clustering by city (i.e., a permutation for TPs in the same city will all be assigned the same implementation status for that time point). Not only does this conservatively account for shared variance that might be present due to being located in the same city, statistical efficiency can be improved by clustered permutation testing. For inference, the test statistic (difference in means) observed based on actual period assignments is compared vis-à-vis the distribution of test statistics using permuted assignments, with the proportion of permuted test statistics greater than the actual observed taken as the one-sided or half of the two-sided p-value. With program measures collected quarterly over 42 months, the number of clustered permutations with 3 study sites (4 cities) is 38,416, allowing testing of statistical significance with  $\alpha < .0001$ . If we permute all 24 TPs independently, tests of significance can be performed with much lower  $\alpha$ . We will conduct both permutation tests with sites permuted independently as well as clustered permutations by city and report the result with the more conservative p-value. Hypothesis testing for Aims 1 and 2—i.e., estimating the effectiveness of the intervention—will involve

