### 3.5. ASSESSMENTS

In addition to the activities described above, BRIDGE will use a few additional assessment tools:

Semi-annual Reports from AC: The research team will request de-identified treatment records of all PWID served by each city's AIDS Center, in a report format prepared by AIDS Center staff twice per year. This allows the research team to compare HIV outcomes between those clients served by a BRIDGE trust point and those served by a non-BRIDGE trust point. For a detailed description of this data collection component, please see the Semi-Annual Report Protocol in Appendix B.

We are also requesting a waiver of informed consent for the Semi-Annual Report from the AIDS Center. As described in more detail in the Semi-Annual Report protocol in Appendix B, BRIDGE study team receive this data in report format once in 6 months, with all personal identifiers removed. The staff in charge of de-identifying this data are those who already have access to it by virtue of their job positions – epidemiologists and treatment specialists at the city AIDS Centers.

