### 3.7. TRUST POINT ELIGIBILITY CRITERIA & SELECTION

Bridge will be carried out at a total of 24 trust points, or 8 per site (3 from Temirtau and 5 from Karaganda will be considered one site). A selection process within each site will identify the “BRIDGE Trust Points” who will carry out the intervention, and the “non-BRIDGE Trust Points” where no intervention will take place.

A multistage site selection process was carried out according to Figure 5:

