**Figure 5: BRIDGE Site Selection Process**

[figure not shown]

[figure not shown]

24 study sites

From the mapping data we collected for this project (conducted under separate IRB protocols AAAQ8761 and AAAQ6156), and by consultation by the Republican AIDS Center the following criteria were determined and will be applied in this trail:

Criterion #1: Trust point must be located within 20km of AIDS Center

This eligibility criterion is important given the large barrier that transportation plays in accessing care. If a trust point is located very far from an AIDS Center, it represents an additional unnecessary barrier to accessing services.

- In Almaty, 1 potential trust point was excluded for not meeting this criterion
- In Shymkent, 8 potential trust points were excluded for not meeting this criterion
- In Karaganda/Temirtau, 3 potential trust points were excluded for not meeting this criterion

Criterion #2: Rapid HIV testing is an existing part of current TP services

Rapid HIV testing must be currently performed in the physical location of the TP (by full-time nurse or staff or by visiting nurse/doctor). If a trust point does not currently perform rapid testing, we will not have adequate pre-intervention data to compare

In Almaty, 2 trust points do not meet this criterion because they do not currently have medical staff – NOT excluded, because they are likely to hire such staff

In Karaganda, 1 trust point does not meet this criterion

Criterion #3: Physical infrastructure of TP: Separate room available for private counselling & testing

Since HIV rapid testing and ARTAS activities require a private space, we have excluded all polyclinics that do not have a room for private consultation with clients. This is based on question from mapping surveys: How many rooms do you have available for private consultations with clients? TPs must report at least one to be included.

In Karaganda, 1 trust point does not meet this criterion

In Shymkent, 1 trust point does not meet this criterion

Criterion #4: Trust point is located in a region which has higher numbers of injection drug users

Prevalence of injection drug use is determined by GHRCCA staff in consultation with the local AIDS Center and Narcology departments. GHRCCA staff makes decisions based on neighborhood characteristics: removed trust points who don't have high prevalence of PWID in the neighborhood.

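### Section 3.5 and Appendix B evaluate Aim 2 by comparing BRIDGE with non-BRIDGE trust points, a non-randomised contrast that conflicts with the pre/post test in section 2.4

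*Combined protocol and SAP*

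**What the plan says.** The combined protocol and SAP describes the Aim 2 comparison in two ways.

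- **Between trust points.** Appendix B (Purpose of Report) ties the semi-annual report to Aim 2 and states: "By comparing epidemiological and laboratory data between BRIDGE trust points and non-BRIDGE trust points, we will be able to evaluate the effects" of implementing BRIDGE in a trust point. Section 3.5 says the report lets the team "compare HIV outcomes between those clients served by a BRIDGE trust point and those served by a non-BRIDGE trust point".
- **Between periods.** Section 2.4 (Data analyses by study aim) says Aim 2 will compare "retention in HIV care, ART initiation, ART adherence, and viral suppression during post-intervention to these same data during pre-intervention". It names the AppSheet system and the semi-annual report as the data sources. The program-data analysis in the same section "will test for differences in outcome measures obtained during the pre-intervention period" and the BRIDGE periods, by permutation test. The paragraph ends by bringing "Hypothesis testing for Aims 1 and 2" under this approach.

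Section 3.7 explains who the comparators are: "A selection process within each site will identify the" trust points that will deliver BRIDGE and those that will not. The second group never receives the intervention, so these are not trust points waiting for their step. Section 2.2 randomises only the timing of roll-out, by city or site.

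On the first selection criterion, location within 20 km of the AIDS Center, section 3.7 says: "This eligibility criterion is important given the large barrier that transportation plays in accessing care".

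**The concern.** The two descriptions estimate different things. The period contrast uses the randomised order of roll-out and compares each trust point with itself. The BRIDGE versus non-BRIDGE contrast compares places that the study team chose with places it did not, and at least one reason for the choice (distance) is one the protocol links to access to care. Retention, ART initiation and viral suppression could differ between the groups before BRIDGE starts.

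If an analyst followed section 3.5 and Appendix B as written, a non-randomised comparison with no stated adjustment would be presented as the effect of the intervention. An analyst who followed section 2.4 would report something else. Both could claim to have followed the protocol.

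**Working it through.** **1. The passages side by side.**

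| Place | Aim 2 contrast | Model or test given |
|---|---|---|
| Section 2.4 | Post versus pre | Permutation test, 24 trust points |
| Section 3.5 | BRIDGE versus non-BRIDGE | None |
| Appendix B | BRIDGE versus non-BRIDGE | None |
| Data Analysis Plan for Primary Study Aim | Does not cover Aim 2 | GLMM/GEE and permutation, primary aim only |

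The only power statement (section 2.4: 80% with 24 trust points, driven by undetectable viral load) concerns the 24 BRIDGE trust points. It cannot be reproduced from the text, which gives no effect size, event rate or ICC values; the figure is not available here, so this is no criticism of the plan. No power is stated for the non-BRIDGE comparison.

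**2. How trust points became BRIDGE or non-BRIDGE (section 3.7).** Itemised exclusions:
- distance: 1 (Almaty) + 8 (Shymkent) + 3 (Karaganda/Temirtau) = 12
- no rapid testing: 1 (Karaganda); 2 in Almaty also failed this criterion but were kept
- no private room: 1 (Karaganda) + 1 (Shymkent) = 2

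Total 12 + 1 + 2 = 15, and 12/15 = 80%; in Shymkent 8 of 9. This takes each entry as a different trust point. Removals for neighbourhood prevalence and unwillingness are not counted in the text, so the true share is unknown.

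**3. What each contrast estimates.** Let δ be the BRIDGE effect, τ the change over time common to both groups, and μ_B and μ_N the baseline levels in BRIDGE and non-BRIDGE trust points.
- Level comparison after roll-out: (μ_B + τ + δ) − (μ_N + τ) = δ + (μ_B − μ_N).
- Unadjusted pre/post within BRIDGE trust points: (μ_B + τ + δ) − μ_B = δ + τ. Period effects, identified by the staggered roll-out, remove τ.
- Difference-in-differences: [(μ_B + τ + δ) − μ_B] − [(μ_N + τ) − μ_N] = δ.

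A constant baseline gap stays in the first and cancels in the other two.

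**4. Illustration of the stakes.** Baseline rate, gap, ICC and number of non-BRIDGE trust points are assumptions. Section 5 expects 1,891 HIV-positive clients at the 24 trust points, so m = 1,891/24 = 78.8 per trust point; the same m is assumed for the comparators. With no BRIDGE effect, a 20% baseline, a 5-point gap favouring selected trust points, ICC 0.05 and 12 comparators:
- design effect = 1 + (78.8 − 1) × 0.05 = 4.89
- effective n: 24 × 78.8/4.89 ≈ 387 versus 12 × 78.8/4.89 ≈ 193
- pooled rate 0.233; SE under the null 0.0373; SE under the alternative 0.0362
- Φ[(0.05 − 1.96 × 0.0373)/0.0362] = Φ(−0.64) = 0.26

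Over ICC 0.01 to 0.10 and 12 to 24 comparators, the probability of a significant pro-BRIDGE result is:

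| Gap | Baseline | Probability |
|---|---|---|
| 5 points | 5% | 0.32–0.99 |
| 5 points | 20% | 0.16–0.79 |
| 5 points | 40% | 0.13–0.65 |
| 2 points | 5% to 40% | 0.05–0.49 |

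The nominal upper tail is 0.025. A gap of the opposite sign would hide a real effect instead.

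**5. Whether the data for a repair exist.** Appendix B covers all HIV-positive PWID at each AIDS Center, lists the client's trust point as a field, and runs every six months from November 2016 to May 2020. Appendix A puts November 2016 at month 13; section 2.2 rolls out in months 22, 28 and 34. The lead times are 22 − 13 = 9, 28 − 13 = 15 and 34 − 13 = 21 months. Every site therefore has at least one complete six-month interval before BRIDGE, and the later two have at least two and three.

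**The case against.** The strongest reply is that the formal Aim 2 test is already the right kind. Section 2.4 sets post versus pre, gives the permutation test and applies it to Aims 1 and 2, while Appendix B mainly describes how a report is prepared. This stands. A reader might infer that Aim 2 rests on the non-BRIDGE comparison alone, or that the randomised timing is thrown away; section 2.4 does not support that.

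Second, neither section 3.5 nor Appendix B says the comparison is of levels at one time. With repeated reports, the wording is compatible with a difference-in-differences. That also stands, but the sentences specify no such analysis, so the gap in the plan remains.

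Third, a reader might infer that the bias must favour BRIDGE. Distance, private space and willingness point that way, but other features could push the other way. Criterion 4 looks for potential recruits rather than people already linked to care. The peer recruitment reaches PWID who never started or left care. The AIDS Center records hold only clients who registered there, so distant clients in the report have already reached care once. The sign is not shown.

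Fourth, a reader might take the whole near/far difference as the bias, or suppose that every non-BRIDGE trust point failed a criterion. If a fraction f of comparison clients attend distant trust points, and the rest resemble BRIDGE clients, a near/far gap g contributes f × g, and f is unknown. In Almaty the top eight by neighbourhood ranking were taken, so a lower-ranked trust point there could meet the other criteria and still be non-BRIDGE.

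**Conclusion.** The concern holds as an unresolved contradiction about the Aim 2 contrast, one side of which is a non-randomised comparison with no adjustment described. Selection on factors plausibly related to care outcomes makes that comparison open to confounding. Neither the size nor the sign can be computed, because no baseline data by trust-point group are given; the probabilities above show only what modest gaps could do under the stated assumptions.

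The cancellation in the within-trust-point and difference-in-differences contrasts assumes that the baseline gap is constant over time. It does not remove a change in client mix brought about by peer recruitment after roll-out. Aim 2 is secondary and a formal pre/post test exists, so this should be fixed before analysis but does not undermine the primary aim.

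**What to change.** - Reword section 3.5 and Appendix B to agree with section 2.4: the Aim 2 effect is the period-adjusted stepped-wedge contrast within the 24 BRIDGE trust points.
- Label the BRIDGE versus non-BRIDGE comparison as supportive only. Analyse it as a difference-in-differences, with trust-point and period effects and a BRIDGE-trust-point by roll-out interaction, using the pre-implementation reports from November 2016.
- Report the baseline differences between the two groups of trust points, including the selection factors.

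The cost is a change of wording in two places, a short addition to the analysis plan and a little analysis. The data are already in the planned semi-annual reports.
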